**Table 9-1 Probability (%) of response for different safety scenarios**

| True event rate (%) | Pr(0/10) | Pr(2+/10) | Pr(0/30) | Pr(2+/30) |
|---------------------|----------|-----------|----------|-----------|
| 1.0                 | 90.4     | 0.4       | 74.0     | 3.6       |
| 3.4                 | 70.0     | 4.6       | 34.3     | 28.3      |
| 5.0                 | 59.9     | 8.6       | 21.5     | 44.6      |
| 10.0                | 34.9     | 26.4      | 4.2      | 81.6      |
| 20.0                | 10.7     | 62.4      | 0.1      | 98.9      |
| 30.0                | 2.8      | 85.1      | <0.1     | >99.9     |
| 40.0                | 0.6      | 95.4      | <0.1     | >99.9     |
| 50.0                | <0.1     | 98.9      | <0.1     | >99.9     |
| 60.0                | <0.1     | 99.8      | <0.1     | >99.9     |

If none of the 130 participants receiving the vaccine experience serious adverse experiences to the vaccine, the exact 95% 2-sided upper confidence bound for the rate of such reactions in the population is 2.8%. Restricted to any of the vaccine arms (n=10) in Part A, the exact 95% 2-sided upper confidence bound for this rate is 31%. Restricted to any of the vaccine arms (n=30) in Part B, the exact 95% 2-sided upper confidence bound for this rate is 12%.

#### 9.4.2 Sample size calculations for immunogenicity

In Part A, the precision with which response rates can be estimated, based on a sample of 10 vaccines, is limited. The standard error of the estimated response rates depends on the true underlying response rate but can be bounded by  $0.16 (= \sqrt{0.5 \times 0.5 / n})$ . Thus, the width of a 95% confidence interval for the response rate in any 1 arm will be no greater than 0.63 (i.e.,  $\pm 1.96 \times 0.16$ ).] In Part B, based on n=30, the standard error of the estimated response rates can be bounded by  $0.09 (= \sqrt{0.5 \times 0.5 / n})$ . Thus, the width of a 95% confidence interval for the response rate in any 1 arm will be no greater than 0.35 (i.e.,  $\pm 1.96 \times 0.09$ ).]

Table 1-2 below displays exact confidence intervals for several possible observed rates of response in Part B.

**Table 9-2 Exact 95% 2-sided confidence intervals for response rates based on observing a particular rate of responses in the vaccinees (n=30) in Part B.**

| Observed response rate(%) | Confidence interval
(n=30) |
|---------------------------|-------------------------------|
| 50                        | [31, 69]                      |
| 60                        | [41, 77]                      |
| 70                        | [51, 85]                      |
| 80                        | [61, 92]                      |
| 90                        | [73, 98]                      |

In Part B, there is limited power for a formal comparison of immunogenicity response rates between vaccine groups of size n=30 and, hence, formal comparisons were not listed in the objectives. For illustration, we include power calculations for comparison of response rates between vaccine groups (n=30) that can be distinguished with statistical power of 80% and 90% for an exact 2-sided test with a Type I error rate of 0.05 in Table 9-3. Note the sizes of the differences the trial is powered to detect are very large.

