**Table 9-3 Minimum detectable differences in response rates between 2 groups (of size 30)**

| True response rate 1 st group (%) | Minimum detectable response rate 2 nd group (%) |           |
|----------------------------------------------|------------------------------------------------------------|-----------|
|                                              | 80% power                                                  | 90% power |
| 10                                           | 44                                                         | 49        |
| 20                                           | 58                                                         | 63        |
| 30                                           | 69                                                         | 74        |
| 40                                           | 78                                                         | 83        |
| 50                                           | 86                                                         | 90        |
| 60                                           | 93                                                         | 96        |
| 70                                           | 98                                                         | >99       |

An alternative to formal comparisons of groups in Part B is to rank the vaccine groups by their immune response rates. We assess the reliability of this study to select the best group

with respect to the magnitude of their response rates. See Table 9-4 below. Each line in the table shows the results of N=40,000 simulated datasets generated using two (best/ next best) different binomial probabilities for 3 groups of size 30, with the best (highest) response probability used to generate data for one group and the next best response probability used to generate data for the remaining 2 groups. These simulations illustrate the probability of correctly selecting the highest response group 90% (or 80%) of the time [101] given the assumed parameters (best response probability, difference between best and next best).

**Table 9-4 Probability of 90% (80%) correct selection of regimen with highest immunology response (n=30 per group) among 3 groups**

| Next Best response probability (%) | Best response probability (%) | Difference |
|------------------------------------|-------------------------------|------------|

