### 9.5.4 Immunogenicity analysis

The statistical analysis for immunogenicity will employ the intent-to-treat principle, i.e., all data from enrolled participants will be used according to the initial randomization assignment regardless of how many injections they received. The only exception will be to exclude data from HIV-infected participants at or post infection. Thus, for HIV-infected participants, only immunogenicity data from samples known to be drawn prior to HIV infection will be included in the analysis.

If assay data are qualitative (i.e., positive or negative) then analyses will be performed by tabulating the frequency of positive response for each assay by vaccine regimen at each time point that an assessment is performed. Binomial response rates will be presented with their corresponding exact 95% confidence interval estimates. For Parts A and B, crude rates for each vaccine group will be calculated. The combined placebo groups of Part B (N=18) will be used to estimate the false positive rate. Although, because of the lack of precision in this estimate, net response rates will not be calculated for the vaccine groups.

To compare the response rates of any two vaccine arms, a significant difference will be declared if the 2-sided 95% confidence interval for the difference in response rates between 2 groups excludes 0. In addition to reporting the point prevalence response rates, cumulative and cumulative repeat (over time/visit) probabilities of cellular immune responses will be estimated with corresponding confidence intervals using maximum likelihood based methods [102]. Missing responses will be assumed to be missing at random, i.e., conditional on the observed data the missingness is independent of the unobserved responses.

For continuous assay variables, overall differences between groups at a specific time point will be tested by a 2-sample t-test if the data appear to be normally distributed, or by utilizing the nonparametric Wilcoxon rank sum test if the data are not normally distributed. If a portion of the measurements are censored below the assay quantification limit, then the Gehan-Wilcoxon test will be employed. More sophisticated analyses employing repeated

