#### **9.5.4.1 Missing data**

If the probability of missing immunogenicity measurements depends on either covariates or on the immunogenicity outcomes of participants, then the methods described above may give biased inferences and point estimates. If a substantial amount of immunogenicity data is missing (at least 1 value missing from more than 20% of participants), then secondary analyses of the immunogenicity endpoints will be conducted using methods that relax the missing completely at random assumption to a missing at random assumption. For a univariate binary and quantitative outcome, respectively, a generalized linear model with a binomial or normal error distribution will be used for estimation and testing. For assessing repeated immunogenicity measurements, linear mixed effects models will be used. The models will be fit using maximum likelihood methods, and will include as covariates all available baseline predictors of the missing outcomes. The longitudinal models will also include all observed immunogenicity data.

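### The stated maximum 95% CI width of 0.35 for a Part B arm is too small (0.36 by normal approximation, 0.37 exact), and the 3.4% row of Table 9-1 holds the values for 3.5%

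*Protocol*

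**What the plan says.** Section 9.4.2 bounds the precision of a response rate in one vaccine arm. For Part B it starts from a maximum standard error: "In Part B, based on n=30, the standard error of the estimated response rates can be bounded by" 0.09. It multiplies this by 1.96 on either side and concludes that "the width of a 95% confidence interval for the response rate in any 1 arm will be no greater than 0.35".

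Table 9-2 follows, titled "Exact 95% 2-sided confidence intervals for response rates based on observing a particular rate of responses in the vaccinees (n=30) in Part B". Its row for an observed 50% gives 31% to 69%, and its row for 60% gives 41% to 77%.

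Section 9.5.4 settles which interval will be reported: "Binomial response rates will be presented with their corresponding exact 95% confidence interval estimates".

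Section 9.4.1 contains Table 9-1, "Probability (%) of response for different safety scenarios", which lists the chance of 0 events and of 2 or more events among 10 and 30 vaccinees. The row for a true rate of 3.4% reads 70.0, 4.6, 34.3 and 28.3.

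**The concern.** An upper bound has to hold in the worst case. This one rests on a standard error rounded below its own maximum, and two rows of the next table exceed it. The sentence gives the Part B precision as a single figure for the secondary, immunogenicity objective, so a reader may take it as the design's guarantee. The width that will appear in the report at a response rate near one half is larger.

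The Table 9-1 row matters in a different way. That table describes how sensitive the trial is to safety events, which is the primary objective, and one row does not match its label.

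**Working it through.** **Inputs.** n = 30 per Part B vaccine arm, worst case p = 0.5, multiplier 1.96 and rounded standard error 0.09 (all Section 9.4.2); exact intervals (Table 9-2 and Section 9.5.4); true rate 3.4% with n = 10 and n = 30 (Table 9-1).

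**Step 1: reproduce the plan's figure.** 2 × 1.96 × 0.09 = 0.3528, printed as 0.35.

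**Step 2: the same formula without early rounding.** The standard error is √(0.5 × 0.5 / 30) = 0.0913, and 2 × 1.96 × 0.0913 = 0.358. The normal-approximation width exceeds 0.35 for 12 to 18 responders out of 30, running from 0.351 to 0.358.

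**Step 3: the exact interval.** For x responders out of n, the Clopper-Pearson limits are the 2.5% quantile of Beta(x, n − x + 1) and the 97.5% quantile of Beta(x + 1, n − x). With n = 30:

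| Responders | Observed rate | Exact limits | Width | Width from the limits printed in Table 9-2 |
|---|---|---|---|---|
| 15 | 50% | 0.313 to 0.687 | 0.374 | 0.38 |
| 18 | 60% | 0.406 to 0.773 | 0.367 | 0.36 |
| 21 | 70% | 0.506 to 0.853 | 0.347 | 0.34 |
| 24 | 80% | 0.614 to 0.923 | 0.309 | 0.31 |
| 27 | 90% | 0.735 to 0.979 | 0.244 | 0.25 |

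The limits in Table 9-2 reproduce. The maximum exact width is 0.374, at 15 of 30. The width is 0.355 to 0.374 for all counts from 10 to 20.

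**Step 4: Part A for comparison.** There the standard error was rounded up, from 0.158 to 0.16, so the stated bound of 0.63 (2 × 1.96 × 0.16 = 0.627) is safe. The exact maximum at n = 10 is 0.626.

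**Step 5: the Table 9-1 row.** Pr(0) = (1 − p)^n and Pr(2+) = 1 − (1 − p)^n − n p (1 − p)^(n−1).

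| True rate | Pr(0/10) | Pr(2+/10) | Pr(0/30) | Pr(2+/30) |
|---|---|---|---|---|
| 3.4%, computed | 70.8 | 4.3 | 35.4 | 27.2 |
| 3.5%, computed | 70.0 | 4.6 | 34.3 | 28.3 |
| Printed against 3.4% | 70.0 | 4.6 | 34.3 | 28.3 |

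All four printed entries match 3.5% and none matches 3.4%. The other rows reproduce.

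**The case against.** The best defence is that this is a rounding slip in a sentence that shows its own arithmetic. On the method it names, the gap is 0.353 against 0.358. The larger gap appears only with the exact interval, and the correct exact limits stand immediately below. Three of the five rows of Table 9-2 lie within 0.35. Section 9.4.2 is also candid that power is limited and that the comparisons are illustrative, and immunogenicity is a secondary objective. All of this is fair, and it sets the weight of the point. It does not make the bound true. The sentence rules out any wider interval, and neither the formula it uses nor the interval to be reported respects that limit. A Wilson interval would (maximum 0.337 at n = 30), but the protocol does not plan one.

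For Table 9-1, the document does not show whether the label or the entries were intended, and a digit misread when the text was taken from PDF cannot be excluded. The row should be checked against the original file first.

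A reader might go further and infer that all Part B precision and power figures are too favourable because samples will be lost before the visit two weeks after the fifth vaccination. The document does not support this as an error. Tables 9-2 to 9-4 state their group size (Table 9-3, for instance, is titled "Minimum detectable differences in response rates between 2 groups (of size 30"), and they reproduce at that size to within 1 point. No attrition rate is given. The threshold in Section 9.5.4.1, "at least 1 value missing from more than 20% of participants", counts a missing value at any time and only triggers secondary analyses. It is not a planning assumption about how many samples will be available at Month 9.5.

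**Conclusion.** The point holds as two small errors of statement.

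- **Width.** The bound of 0.35 for a Part B arm is wrong by about 0.01 on the normal approximation (0.358) and about 0.02 on the prescribed exact interval (0.374). Two rows of Table 9-2 contradict it.
- **Table 9-1.** The 3.4% row differs from the correct values by 0.3 to 1.1 percentage points.

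The width results assume 30 evaluable vaccinees, as the protocol does, and take exact to mean Clopper-Pearson, which reproduces Table 9-2. The Table 9-1 result assumes that the label was read correctly from the PDF.

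Nothing here bears on the sample size, the planned analyses or the Part A bound, and it does not show that Tables 9-2 to 9-4 are wrong.

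**What to change.** In Section 9.4.2, replace 0.35 by 0.37 and say that it refers to the exact interval, which matches Table 9-2 and Section 9.5.4. If the normal approximation is kept, write 0.36 and carry the standard error as 0.0913.

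In Table 9-1, after checking the original file, either relabel the 3.4% row as 3.5% or keep the label and enter 70.8, 4.3, 35.4 and 27.2.

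Both are text edits, with no effect on participants, conduct or analysis. Showing precision for fewer than 30 evaluable vaccinees would be an optional addition resting on an assumed loss, and this point does not require it.

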## 1.3 Cytokine-augmented DNA vaccination

The safety and partial efficacy of DNA vaccination in nonhuman primate studies has led to a number of approaches to augment the efficacy of this vaccine modality. One such strategy

involves the boosting of a DNA-primed immune response with a recombinant live vector. A second promising strategy involves the coadministration of plasmid-encoded immunomodulator molecules. Augmentation of DNA vaccine–elicited HIV-specific cellular immune responses in mice has been reported by a number of laboratories using plasmids expressing GM-CSF, IL-2, CD40L, IL-12, IL-15, B7-2, ICAM-1, LFA-3, RANTES, MIP-1 alpha, or MCP-1 [31-35].

Cytokines are molecules secreted mainly by bone marrow–derived cells that act in an autocrine or paracrine manner to induce a specific response in cells expressing the appropriate cytokine receptor. Recent vaccine strategies have attempted to incorporate cytokine-expressing plasmids with the viral genes of interest in efforts to elicit cell-mediated immune responses. Initial murine studies have shown that both GM-CSF and *IL-12* plasmids were able to enhance CTL responses to a peptide-based vaccine [36]. Subsequent studies evaluating plasmids encoding GM-CSF or *IL-12* have shown enhancement of CTL responses [37-39], and protection from disease after vaccinia challenge [40]. While there are few published studies evaluating vaccine immunogenicity in primates, van der Meide *et al.* found that recombinant *IL-12* augmented cellular immune responses in a macaque model [41].

These published studies, in combination with the preliminary results summarized in this protocol, provide the rationale to pursue HIV *gag* and *IL-12* plasmid–based vaccines in this first in human study to determine whether DNA encoding IL-12 is safe, and whether it provides an adjuvant effect designed to augment HIV-specific CTL responses.

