### 9.4 Accrual and sample size

Recruitment will target 156 healthy, HIV-uninfected adult participants.

Part A will consist of 4 groups. Groups 1 and 2 will be enrolled simultaneously with participants randomized to receive either *gag* DNA or placebo (Group 1), or *gag* DNA plus *IL-12* DNA (100 mcg) or placebo (Group 2) in a (10:2) ratio within each group. Groups 3 and

4 will proceed sequentially according to dose escalation rules outlined in Sections 8.3 and 14.7.5. Groups 3 and 4 will each enroll participants randomized to receive either *gag* DNA plus *IL-12* DNA (maximum tolerated dose, MTD) or placebo in a (10:2) ratio.

Part B will consist of 3 groups (Groups 5, 6, 7) and will follow Part A according to rules outlined in Section 8.4. Groups 5, 6, and 7 will be enrolled simultaneously and randomized to receive either *gag* DNA (1500 mcg) for both prime and booster vaccinations or placebo (Group 5), or *gag* DNA plus *IL-12* DNA (MTD) for both prime and booster vaccinations or placebo (Group 6), or *gag* DNA plus *IL-12* DNA (MTD) for prime and HIV CTL MEP for booster vaccinations or placebo (Group 7), each group with a (30:6) ratio for vaccine to placebo.

Note that study design blinds participants and site staff to vaccine or placebo arms of each group, but participants will not be blinded as to which group they are in.

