#### 9.4.1 Sample size calculations for safety

The goal of the safety evaluation for this study is to identify safety concerns associated with administration. Sample size calculations for safety are expressed in terms of the ability to detect rare events (e.g. serious adverse events (SAEs)).

The ability of the study to identify serious adverse experiences can be expressed by the maximum true rate of events that would be unlikely to be observed and the minimum true rate of events that would very likely be observed.

Specifically, for each vaccine arm of Part A (n=10), there is a 90% chance of observing at least 1 serious adverse experience if the true rate of such an event is at least 21%; there is a 90% chance that we would not observe at least 1 serious adverse experience if the true rate was no more than 1%.

For each vaccine arm of Part B (n=30), there is a 90% chance of observing at least 1 serious adverse experience if the true rate of such an event is at least 8%; there is a 90% chance that we would not observe at least 1 serious adverse experience if the true rate was no more than 0.35%.

Probabilities of observing 0 or 2 or more serious adverse experiences among groups of size 10 and 30 are presented in Table 9-1 for a range of possible true event rates. These calculations provide a more complete picture of the sensitivity of this study design to identify potential safety problems with the vaccine.

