### **13.2.12 Preparation of HIV *gag* DNA Plasmid 1500 mcg / IL-12 DNA 1500 mcg or Placebo (Groups 6 and 7)**

*HIV gag DNA Plasmid 1500 mcg / IL-12 DNA 1500 mcg*

All vials should be visually inspected prior to use. If any vial contains material different from its description above, do not use the vial and contact the protocol pharmacist. Using aseptic technique, the pharmacist will use a 3 mL syringe to withdraw 0.9 mL of HIV *gag* DNA Plasmid 2 mg/mL vial. The contents of this syringe will then be slowly injected into the vial containing 0.9 mL of *IL-12* DNA (2 mg/mL) (Lot # 76180001A). The pharmacist should avoid creating bubbles. To prevent aerosolization, the pharmacist should, before removing the needle from the vial, bring the needle above the level of the liquid and allow excess air to rise into the syringe. Remove the syringe from the vial and discard into a sharp's container. The pharmacist will mix the solution in the vial by gentle swirling (avoid creating bubbles). The final product should be a clear colorless liquid containing 1.8 mL of a 1:1 mixture of HIV *gag* DNA Plasmid: *IL-12* DNA, consisting of 1000 mcg/mL of HIV *gag* DNA and 1000 mcg/mL of *IL-12* DNA. Using a new 3 mL syringe, the pharmacist will withdraw 1.5 mL of this final product. The pharmacist will label the syringe as HIV *gag* DNA Plasmid 1500 mcg / *IL-12* DNA 1500 mcg or placebo. The final product must be administered within 4 hours after preparation. It must be stored at 2 to 8°C if not administered immediately after preparation.

*Any unused portion of entered vials and expired pre-filled syringes should be disposed of in accordance with institutional or pharmacy policy.*

*Placebo (for HIV gag DNA Plasmid 1500 mcg / IL-12 DNA 1500 mcg)*

Using aseptic technique, the pharmacist will withdraw 1.5 mL of sodium chloride injection USP, 0.9% into a 3 mL syringe. The pharmacist will label the syringe as HIV *gag* DNA Plasmid 1500 mcg / *IL-12* DNA 1500 mcg or placebo. The final product must be administered within 4 hours after preparation. It must be stored at 2 to 8°C if not administered immediately after preparation.

*Any unused portion of entered vials and expired pre-filled syringes should be disposed of in accordance with institutional or pharmacy policy.*

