Based on the number of responders observed at the primary immunogenicity timepoint (in *italic* in Visit 11), humoral and cellular assays may be performed on all participants, including Visits 7 and 13.

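### Groups 6 and 7 have identical priming until vaccination 4, but Part B is summarised per arm of 30 and Group 7's priming reactions are merged with its boost reactions

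*Protocol*

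**What the plan says.** - **Allocation.** Protocol 9.4: "Groups 5, 6, and 7 will be enrolled simultaneously and randomized to receive either" gag DNA alone (Group 5), gag plus IL-12 DNA for prime and boost (Group 6), or the same prime with a peptide boost (Group 7). Each group has 30 vaccine and 6 placebo recipients.
- **Priming product.** Protocol 13.2.12 gives a single preparation for both groups, "DNA Plasmid 1500 mcg / IL-12 DNA 1500 mcg or Placebo (Groups 6 and 7"), from one IL-12 DNA lot. Section 13.1 gives both the same volume (1.5 mL) and schedule (Months 0, 1, 3). They diverge at vaccination 4, Month 6.
- **Safety sizing.** Protocol 9.4.1: "For each vaccine arm of Part B (n=30), there is a 90% chance of observing at least 1 serious adverse experience" if the true rate is at least 8%. The upper bound for zero events in 30 is given as 12%. The only larger denominator is all 130 vaccinees, with a bound of 2.8%.
- **Safety analysis.** Protocol 9.5.3 tabulates reactogenicity by vaccine regimen, one count per participant at the worst severity over all injection visits. Adverse experiences are also counted once per participant, with no priming window.
- **Immunogenicity.** Protocol 9.4.2: "In Part B, there is limited power for a formal comparison of immunogenicity response rates between vaccine groups of size n=30". Section 9.5.4 gives rates per vaccine group and compares pairs of arms. ELISpot and ICS are planned at baseline and two weeks after the fifth vaccination (8.7.3). Depending on responders at that time point, Appendix C says that "humoral and cellular assays may be performed on all participants, including Visits 7 and 13". Anti-IL-12 antibody and tetramer assays two weeks after the third vaccination carry no such condition (8.7.4.2, 8.7.4.3).

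**The concern.** Neither IL-12 plasmid has been given to humans (Protocol 4.2), and safety is the primary objective. Section 1.3 asks whether IL-12 DNA is safe and "whether it provides an adjuvant effect designed to augment HIV-specific CTL responses". The randomised priming contrast, 60 on gag plus IL-12 DNA against 30 on gag DNA alone, addresses both questions without confounding by the boost. The plan does not use it.

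The reactogenicity rule makes this more than an unused option. A severe reaction in Group 7 could come from IL-12 DNA priming or from the peptide/RC529-SE/GM-CSF boost, and the planned table would not show which. The boost may well be reactogenic: Table 4-1, on blinded data from the peptide trial with N=52, lists 47 entries of injection-site pain or tenderness (17 mild, 28 moderate, 2 severe). As specified, the only Part B summary of IL-12 DNA reactogenicity free of peptide reactions is Group 6, 30 people over five doses.

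**Working it through.** **Inputs.** 30 vaccinees per Part B group (9.4); identical priming in Groups 6 and 7, so 30 + 30 = 60; two-sided exact test at 0.05 (9.4.2).

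**Safety.** True rate giving a 90% chance of at least one event: 1 − 0.1^(1/n). Upper limit of the exact two-sided 95% interval for zero events: 1 − 0.025^(1/n). Chance of at least one event at true rate p: 1 − (1 − p)^n.

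| Quantity | Protocol, n=30 | Recomputed, n=30 | Pooled priming, n=60 |
|---|---|---|---|
| Rate for 90% chance of ≥1 event | 8% | 7.4% | 3.8% |
| Upper bound, zero events | 12% | 11.6% | 6.0% |
| Chance of ≥1 event at true 5% | 78.5% (100 − 21.5, Table 9-1) | 78.5% | 95.4% |
| Chance of ≥2 events at true 5% | 44.6% (Table 9-1) | 44.6% | 80.8% |

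The protocol's n=30 figures reproduce, allowing for rounding up. Pooling roughly halves the first two rows.

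**Adjuvant effect.** Power of the two-sided Fisher exact test by full binomial enumeration; the entries are the lowest second-group response rate (%) reaching 80% power.

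| Group 5 rate | Table 9-3 | Recomputed 30 v 30 | 30 v 60 |
|---|---|---|---|
| 10 | 44 | 43.7 | 37.0 |
| 20 | 58 | 57.6 | 50.7 |
| 30 | 69 | 68.3 | 61.3 |
| 40 | 78 | 78.0 | 71.5 |
| 50 | 86 | 85.8 | 80.2 |
| 60 | 93 | 92.4 | 87.5 |
| 70 | 98 | 98.0 | 93.7 |

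Table 9-3 reproduces. The reduction runs from 98.0 − 93.7 = 4.3 points to 68.3 − 61.3 = 7.0 points. Power at Table 9-3's own 80% alternatives rises from 80.3–82.5% to 93.1–96.9%.

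The gain is limited because Group 5 does not grow. With equal variances, the ratio of standard errors of the difference is √[(1/30 + 1/60) / (1/30 + 1/30)] = √0.75 = 0.866, a fall of about 13%.

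**The case against.** The other side has good points, and most of them set limits on this one.

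- **The sentence in 9.4.2 is correct.** The Part B ELISpot and ICS time point follows the fifth vaccination, when Groups 6 and 7 differ. Part B is described as a regimen selection design (5.1), and the objectives are framed as prime plus boost. A reader might infer that n=30 is an error; at that time point it is not.
- **Nothing is lost.** A reader might infer that half the IL-12 DNA data are discarded. All 60 participants are followed, nothing forbids pooling, and an unseen SAP could add it. This stands against any claim of lost data. It does not answer the reactogenicity rule, which the protocol itself fixes in a form that merges prime and boost.
- **The safety figures are not like for like.** The 8% and 12% figures cover the full regimen over 15 months; 3.8% and 6.0% cover three doses up to vaccination 4. They can supplement the n=30 figures but not replace them, since five-dose gag plus IL-12 DNA exposure remains 30.
- **Other safety pooling exists.** There is the 130-vaccinee bound and the Safety Monitoring Board's aggregate review of vaccine against placebo. Neither isolates IL-12 DNA recipients. Part A adds 30, of whom 10 are at 1500 mcg, on the other IL-12 plasmid lot.
- **Post-prime assays are partly planned.** A reader might infer that nothing is measured after priming unless Visit 11 shows responders. That applies only to ELISpot and ICS. Making those two unconditional would use blood already scheduled, but it is a resource choice on secondary endpoints that the documents do not compel.
- **Group assignment is open.** Participants know their group (7, 9.4), so subjective reactogenicity in Groups 6 and 7 against Group 5 is open to expectation effects. This stands.

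**Conclusion.** The point holds as a low-cost improvement to the analysis. Groups 6 and 7 are one concurrently randomised set of 60 until vaccination 4. The planned Part B summaries do not use this, and the all-visits maximum-severity rule hides priming reactions in Group 7.

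For priming safety, the detectable rate and zero-event bound roughly halve (7.4% to 3.8%; 11.6% to 6.0%). For the adjuvant contrast the gain is modest: 4 to 7 points and about 13% in standard error. Detectable differences remain large, for example 10% against 37%, so the protocol's caution about power still applies.

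These figures assume that all 60 vaccinees contribute priming data. The comparison figures also assume an assay result from everyone; tetramer assays depend on HLA type and could have fewer. Pooling is valid only before vaccination 4.

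**What to change.** - **9.5.3:** add a priming-phase summary, covering reactogenicity after vaccinations 1 to 3 and adverse events before vaccination 4, with Groups 6 and 7 pooled (n=60) beside Group 5 (n=30). Note that subjective symptoms are compared with group known.
- **9.4.1:** add the n=60 priming-phase figures (3.8% and 6.0%) as a supplement, keeping the n=30 full-regimen figures.
- **9.5.4:** for post-third-vaccination assays that are performed, compare pooled Groups 6 and 7 with Group 5. Anti-IL-12 antibody and tetramer are already planned; include ELISpot and ICS if Visit 7 is assayed.
- **After vaccination 4:** analyse the groups separately, as now planned.

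The cost is wording and a few extra tables, with no added participants, blood or required assays.
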